## Abstract

**Background:**

Functional dyspepsia (FD) is a prevalent gastric disorder that is difficult to manage due to lack of satisfactory treatments. Acupuncture has been studied with regard to the rising need for treating FD, but the mechanism verifying its efficacy has not yet been fully revealed. The aim of this study is to explore the efficacy and mechanism of acupuncture for FD compared with a sham group.

**Methods/design:**

We describe a proposal for a randomized, assessor-blind, sham-controlled trial with 70 eligible participants who will be randomly allocated either into an acupuncture or a sham group. Participants in the acupuncture group will receive 10 sessions of real acupuncture treatment and those in the sham group will be treated with identical sessions using a Streitberger needle. Functional magnetic resonance imaging (fMRI) and metabolomics studies will be implemented before and after 4 weeks of treatment to investigate the mechanism of acupuncture. The primary outcome is a proportion of responders with adequate symptom relief and the secondary outcomes include the Nepean Dyspepsia Index - Korean version, Functional Dyspepsia-Related Quality of Life questionnaire, Ways of Coping Questionnaire, Coping Strategies Questionnaire, perception of bodily sensation questionnaire, State-Trait Anxiety Inventory, and the Center for Epidemiological Studies - Depression Scale. The outcomes will be evaluated before and after the treatment.

**Discussion:**

This is the first large-scale trial evaluating the efficacy and mechanism of acupuncture with fMRI and metabolomic methods. We will compare real acupuncture with the Streitberger sham needle to verify the specific effect of acupuncture. The results of this trial are expected to be relevant evidences affecting policy and decision-makers associated with routine healthcare.

**Trial registration:**

ClinicalTrials.gov Identifier: NCT02358486.

Date of Registration: 21 January 2015.

## Background

Functional dyspepsia (FD) is a common gastrointestinal disorder that is defined as persistent or recurrent abdominal pain or discomfort centered in the upper abdomen that occurs in the absence of any structural lesion [1]. The prevalence of FD varies from 11 % to 29.2 % globally [2], and recently more than 40 % of patients who visited hospitals in South Korea have been diagnosed with FD [3]. The conventional treatments for FD include antisecretory agents, prokinetics, and antidepressant agents [4]. However, owing to the unsatisfactory efficacy of these approaches, patients with FD often turn to alternative and complementary therapies such as acupuncture [5]. Acupuncture has been used in Asia for centuries to treat FD. During the past decade, many clinical and experimental research studies have revealed that acupuncture reduces gastric symptoms, such as abdominal distension, epigastric pain, and belching [6–8]. A recent meta-analysis on acupuncture for FD reported that there was a lack of robust evidence on the efficacy and safety of acupuncture, which might be due to the poor quality of previous studies [9]. The mechanism and efficacy of acupuncture is still not fully understood, and high-quality studies with a suitable design for acupuncture are needed.

Positron emission tomography (PET) and functional magnetic resonance imaging (fMRI) are promising techniques for exploring the central mechanism of acupuncture [10]. A recent study indicated that the regional and distant connectivity of the anterior cingulate cortex and thalamus are correlated with the severity of FD [11]. Authentic and sham acupuncture procedures have relatively different brain responses in the insula and hypothalamus [12]; therefore, an emphasis has recently been placed on differentiating the brain areas activated during acupuncture.

Metabolomics is defined as the systematic study to measure the multi-parametric metabolic response of a living system to pathophysiological stimuli or genetic modification quantitatively [13, 14]. In contrast to the reductionism of modern medicine, a metabolomic study approaches from the viewpoint of a living organism in systemic way, which corresponds with the traditional Korean medicine (TKM) theory that focuses on holistic treatment. In addition, changes in metabolites reflect the response of the biological system; therefore, metabolomics could provide insights about possible mechanisms underlying the effects of acupuncture. A recent nuclear magnetic resonance (NMR)-based metabolomics study showed the potential biological effect of acupuncture on FD [15]; however, there are some limitations, and the scientific evidence is still insufficient.

Considering these features, a randomized, assessor-blind, sham-controlled clinical trial is planned to investigate the effect of acupuncture on FD. To analyze the mechanism of acupuncture, fMRI will be used in the study to identify the differences between the sham and acupuncture groups and their influence on clinical outcomes. We will also use 1H NMR-based metabolomics to characterize the difference in the metabolic profiles of the plasma and the urine of FD patients in the acupuncture group compared with the sham control group.

## Methods/design

### Objectives

The aims of this study are as follows:Investigate whether manual acupuncture brings adequate relief of FD symptoms in comparison with the sham control group.Determine the difference of brain activity between the real and sham acupuncture groups and the correlation between brain and clinical outcomes.Assess any correlation between differences and changes in the metabolite and clinical outcomes.

### Hypothesis

We hypothesized that 10 sessions (4 weeks) of acupuncture treatment will improve FD symptoms, and a mechanistic difference will exist between the acupuncture and the sham control for FD based upon the fMRI and the metabolomics study.

### Design

A randomized, assessor-blind, sham-controlled trial will be performed at the Kyung Hee University Hospital at Gangdong in Seoul, Korea, beginning in January 2015. The flow of the entire trial is shown in Fig. 1.

**Fig. 1 Fig1:**
[figure not shown]
Flow of the study

### Ethical considerations

This trial will be carried out along with the protocol approved by the Institutional Review Board (IRB) of the Kyung Hee University Hospital at Gangdong (KHNMCOH 2014-08-002-002), the standards of the International Committee on Harmonization on Good Clinical Practice, and the revised version of the Declaration of Helsinki. The purpose and risks of the trial will be fully explained to the participants, who will be required to provide informed consent to indicate that they agree with the protocol and would take part in the trial. The participants will be able to quit at any time during the study period. Any financial costs incurred due to adverse events related to the trial will be covered for the participants. This trial is registered at ClinicalTrials.gov (NCT02358486).

### Inclusion and exclusion criteria

The inclusion and exclusion criteria are based on a previous study [16].

#### Inclusion criteria

The inclusion criteria are as follows:Age between 30 and 49 years.Meeting the definition of FD and postprandial distress syndrome (PDS) as a subtype of FD according to the Rome III criteria [17].Complaints of a degree of dyspepsia that produces a score of more than 40 points on the visual analog scale (VAS; 0, no symptom at all; 100, the most severe symptom one has ever had).Answer at least three questions worth more than 2 points on the Gastrointestinal Impact Scale.Have normal esophagogastroduodenoscopy results within a year and no evidence of any organic diseases.Individuals who are not supposed to take any other treatments associated with FD during the study.

#### Exclusion criteria

Participants with the following characteristics will be excluded:Individuals who have obvious organic diseases such as reflux esophagitis.Individuals who have apparent signs of irritable bowel syndrome.Individuals who have alarming symptoms (weight loss, black or tarry stool, or dysphagia).Individuals who have serious internal organ diseases (diseases of the heart, lung, liver, or kidney) or mental illness.Individuals who have undergone surgery related to the gastrointestinal tract.Individuals who are pregnant or breastfeeding.Individuals who are taking drugs that could affect the gastrointestinal tract; a minimum wash-out period of 2 weeks is required before participating in the trial.Individuals who are positive for human immunodeficiency virus infection.Individuals who have severe problems due to malabsorption.Individuals who have difficulties in attending the trial (for example, due to paralysis, serious mental illness, dementia, drug addiction, time constraints, severe disorder of vision or hearing, or illiteracy).Individuals with other issues that could interfere with acupuncture treatment (for example, clotting disorders or leukopenia, a pacemaker, epilepsy, or anticoagulant therapy).Individuals who have metal implants or fragments that might influence the fMRI examination.

### Recruitment

Banner advertisements will be placed on the notice boards in the hospital. We will run classified advertisements on web sites that patients with digestive problems often visit. We will place the advertisements in the local newspaper and at the bus and subway stations.

### Intervention

Detailed information regarding the acupuncture treatment is described in the form of the revised STandards for Reporting Interventions in Clinical Trials of Acupuncture (STRICTA) [18] listed in Table 1. Thirteen acupoints that are widely used to manage digestive symptoms are selected [19, 20]. The treatment will last for 20 minutes each visit, and a total of ten treatment session will be implemented, including two sessions during the MRI scanning.

**Table 1 Tab1:** Acupuncture treatment details based on the STRICTA 2010 checklist

Item	Detail
1. Acupuncture rationale	1a) Style of acupuncture
	- Manual acupuncture based on traditional meridian theory.
	1b) Reasoning for treatment provided, based on historical context, literature sources, and/or consensus methods, with references where appropriate
	- Manual acupuncture treatments based on the traditional meridian theory, clinical experience, and consensus by the experts in acupuncture and FD.
	1c) Extent to which treatment was varied
	- No additional acupoints allowed.
2. Details of needling	2a) Number of needle insertions per subject per session (mean and range where relevant)
	- Fixed 13 acupoints.
	2b) Names (or location if no standard name) of points used (uni/bilateral)
	- LI 4, ST36, LR3, PC3, SP4, and ST34 (bilateral) and CV12 (unilateral).
	2c) Depth of insertion, based on a specified unit of measurement or on a particular tissue level
	- From 5 to 30 mm.
	2d) Response sought (for example, de qi or muscle twitch response)
	- De qi sensation
	2e) Needle stimulation (manual, electrical)
	- Manual stimulation: needle rotation with thumb and index fingers at 3 Hz.
	2f) Needle retention time
	- Fifteen minutes.
	2 g) Needle type (diameter, length, and manufacturer or material)
	- A sterilized stainless steel needle (0.2 × 40 mm, Dongbang Acupuncture Inc., Ungcheon, Boryeong, Korea).
3. Treatment regimen	3a) Number of treatment sessions
	- Ten treatment sessions in both groups including two sessions during fMRI scanning.
	3b) Frequency and duration of treatment sessions
	- Twice weekly for 4 weeks plus additional two treatments during fMRI scanning (before and after treatment), 15 minutes for each session.
4. Other components of treatment	4a) Details of other interventions administered to the acupuncture group (moxibustion, cupping, herbs, exercises, lifestyle advice)
	- No other interventions during the study period allowed.
	4b) Setting and context of treatment, including instructions to practitioners, and information and explanations to patients
	- Participants will be informed that the acupuncture treatment is based on traditional Korean medicine and previous studies on clinical trial.
5. Practitioner background	5) Description of participating acupuncturists (qualification or professional affiliation, years in acupuncture practice, other relevant experience)
	- Korean medicine doctors who have license and at least 3 years of experience of treating gastrointestinal diseases. They have studied acupuncture for more than 10 years and graduated from a university of Korean medicine. To ensure providing identical treatments, they finished 10 hours of training and simulated the protocol.
6. Control or comparator interventions	6a) Rationale for the control or comparator in the context of the research question, with sources that justify this choice
	- Streitberger needle will be used as a sham control (its rationale is described in background and discussion of main text).
	6b) Precise description of the control or comparator. If sham acupuncture or any other type of acupuncture-like control is used, provide details as for items 1 through 3 above.
	- Practitioners will use identical acupoints to sham group compared with real acupuncture group.
	- The depth of insertion, response sought, needle stimulation, needle retention time, treatment period, and number of treatment sessions in sham group will be the same as those in real acupuncture group.
	- In sham acupuncture group, Streitberger placebo needles (0.2 × 40 mm, Asia Med GmbH, Germany) will be used.

*STRICTA* STandards for Reporting Interventions in Clinical Trials of Acupuncture, *FD* functional dyspepsia, *LI* large intestine, *ST* stomach, *LR* liver, *PC* pericardium, *SP* spleen, *CV* conception vessel

### fMRI scanning procedure

fMRI data will be acquired using a 3 T Philips Achieva MRI scanner (Philips Medical System, Best, the Netherlands) equipped for echo planar imaging with an 8-channel head coil. A whole-brain T2*-weighted gradient echo blood oxygenation level-dependent (BOLD) pulse sequence (repetition time [TR]/echo time [TE] = 2000/35 ms, flip angle = 90°, 34 axial slices, voxel size = 2.87 × 2.87 × 4 mm^3^) will be used. In addition to the fMRI data, we will collect structural data using a T1-weighted 3D turbo field echo (TR/TE = 9.9/4.6 ms, flip angle = 8°, voxel size = 1 mm isotropic). Patients will be asked to lay supine in the scanner while wearing earplugs to attenuate the gradient noise.

Patients will participate in three sessions on the same day: a training session, a nutrition drink test session, and an imaging session. The training session is intended to familiarize the subjects with the modified pressure algometer (MA) and the rating procedures. For the nutrition drink test session, we will induce postprandial symptoms and determine pressures to produce appropriate abdominal discomfort to be used during the subsequent imaging session.In the training session, we will introduce our pressure-induced discomfort stimuli and rating procedures. A series of 14-second pressure stimuli will be delivered to the epigastric area using an MA connected to a rapid cuff inflator system (Hokanson E20, AG101, Bellevue, WA, USA). This rapid cuff inflation system allows us to set an accurate pressure within 1 mmHg. Using this system, the target pressure can be reached in 2 seconds, and we can deflate the pressure immediately. Subjects will be asked to verbally rate their pressure-induced discomfort using a 0–100 numerical scale, where 0 is labeled “no discomfort” and 100 is labeled “the worst discomfort, but not painful.” We will set the abdominal pressure to target a discomfort intensity of about 60/100 as “moderate discomfort.” The pressure required to induce a 60/100 discomfort intensity (D60) and discomfort symptoms from the abdominal pressure will be recorded during the training session.In the nutrition drinking test session, subjects will be asked to consume canned drinks in the morning after an overnight fast. We will use the same procedures as those described in a previously reported protocol [21]. Subjects will consume 200 mL of Newcare (Welife, Cheonan, Republic of Korea), which contains 1 kcal/mL with 20 g of carbohydrates, 6 g of fat, and 7 g of protein. Subjects will drink a can every 4 minutes until they reach a predetermined maximum level of fullness. At 4-minute intervals, the subjects will verbally rate their overall fullness levels on a range of 0–5 (0: no fullness, 1: the first sensation of fullness, 2: mild, 3: moderate, 4: severe, and 5: unbearable fullness). The participants will be instructed to stop drinking when their fullness reaches a level of 4. The actual volume of the canned drinks consumed up until this point is the maximum tolerable volume. Questionnaires for postprandial symptoms, intensity of abdominal discomfort, and abdominal pressure for the D60 will be administered 15 minutes after participants complete the test. The regained pressure for D60 at this point will be used during the imaging session.In the imaging session, fMRI data will be acquired for the meal-loaded discomfort resting state run (REST), continuous pressure stimuli run (CONT), and block design pressure stimuli run both before acupuncture (TASK1) and after acupuncture (TASK2). Following each scan, the subjects will be asked to verbally rate their discomfort intensity and fullness level after each run using the same scales (a 0–100 scale for the discomfort intensity, a 0–5 scale for the fullness level) as previously instructed during the training and nutrition drinks test sessions.

For runs in both the REST and CONT runs, subjects will be instructed to relax and lie still with their eyes open. The REST is a 6-minute run, and subjects with abdominal discomfort induced by the nutrition drink test, as described above, will be allowed to rest without pressure stimuli. The CONT (continuous MA-induced discomfort state) lasts for 7 minutes, and a constant and individually tailored pressure (D60) will be delivered to each subject.

Both TASK1 and TASK2 runs will consist of a block design with seven 14-second stimulation blocks (ON) interspersed between eight 30-second rest blocks (OFF). The total time for the block design run is 5 minutes and 20 seconds. For the stimulation blocks, we will use the same D60 pressure level, which is predetermined from the nutrition drinks test session. The subjects will be instructed to use a button during the TASK runs to indicate when the pressure-induced discomfort is not decreasing after the abdominal pressure stimulation ends. Either real or sham acupuncture will be applied after the TASK1 run, and 15 minutes of retention time will be given to gain a sufficient acupuncture effect. The TASK2 run will be followed by the acupuncture treatment and structural data collection. The entire imaging session procedure is summarized in Fig. 2.

**Fig. 2 Fig2:**
[figure not shown]
Functional magnetic resonance imaging experiment paradigm (REST, meal-loaded steady-state resting run; CONT, continuous MA steady-state run; TASKT1/2, block design MA stimulus run; T1, structural image acquisition; ACUP, acupuncture treatment; MA, modified pressure algometer)

### fMRI data processing

Functional MRI data will be processed using the FSL (FMRIB Software Library; http://fsl.fmrib.ox.ac.uk/fsl), AFNI (Analysis of Functional NeuroImages; https://afni.nimh.nih.gov/afni), and FreeSurfer (http://freesurfer.net) software packages. Data will be corrected for physiological artifacts, slice timing, and affine head motion, and non-brain extraction will also be performed. Cortical surface reconstruction will be carried out to improve structural-functional co-registration using FreeSurfer’s bbregister tool, and then the data will be registered to the standard Montreal Neurological Institute (MNI) space. Spatial smoothing and temporal filtering will be applied.

We will determine the functional connectivity for the data from the REST and CONT runs using seed correlation analysis and independent component analysis. For the seed correlation analysis, seeds will be defined based on the block design runs results (TASK1 and TASK2) and other discomfort/visceral stimulation fMRI studies [22–25]. For the TASK runs, statistical parametric mapping at the single subject level will be carried out using a generalized linear model (GLM) with a stimulation block design and discomfort as the explanatory variables. In order to investigate the link between discomfort-induced brain functions and behavioral/clinical measures, we will perform a whole-brain voxel-wise linear analysis. All brain maps will be thresholded using a cluster correction for multiple comparisons at a z score > 2.3 and a cluster size threshold of *p* < 0.05.

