### Statistical analysis

A statistical analysis will be conducted by an independent statistician using SPSS 16.0 (SPSS Inc., Chicago, IL, USA). All continuous variables will be presented as means and SDs, and categorical variables will be shown as a number (%). All analyses will be based on the intention-to-treat principle using the last observation carried forward rule. The statistical significance level will be considered to be 0.05 (two-sided) with 95 % confidence intervals (CI). When continuous variables are compared between two groups, a two-sample *t*-test (parametric method) or Mann–Whitney *U* test (non-parametric method) will be used. The paired *t*-test (parametric method) or Wilcoxon signed ranks test (non-parametric method) will be used to compare continuous variables both before and after the treatment. When the variable is categorical, a chi-square test or Fisher’s exact test will be implemented. If there are statistically significant differences between groups, an analysis of covariance (ANCOVA) or logistic regression will be used.

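### The fMRI part of the mechanistic hypothesis has no named contrast, and multiplicity is corrected only within each brain map, so the chance of some false real-versus-sham map is well above 5%

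*Protocol article*

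**What the plan says.** The Hypothesis section of the protocol article states that "a mechanistic difference will exist between the acupuncture and the sham control for FD based upon the fMRI and the metabolomics study". The second aim under Objectives is to "Determine the difference of brain activity between the real and sham acupuncture groups and the correlation between brain and clinical outcomes". Neither place names a brain region, run or contrast.

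The fMRI data processing section describes the analyses. It will determine "functional connectivity for the data from the REST and CONT runs using seed correlation analysis and independent component analysis". The numbers of seeds and components are not given, and the choice of seeds is partly left to the trial's own data: "seeds will be defined based on the block design runs results (TASK1 and TASK2) and other discomfort/visceral stimulation fMRI studies". The TASK runs go through a model with two explanatory variables, stimulation block and discomfort, described at single-subject level. A whole-brain voxel-wise analysis then links brain function to behavioural and clinical measures. Table 1 places scans before and after treatment, and the Discussion wants both short-term and longitudinal effects.

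Error control for all of this is one sentence: "All brain maps will be thresholded using a cluster correction for multiple comparisons". The limits it sets are z above 2.3 to form clusters and p below 0.05 for their size. The Statistical analysis section sets a general two-sided level of 0.05 and says nothing further about imaging.

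**The concern.** A cluster correction controls the chance of a false cluster somewhere in one map. It does not control the chance of a false cluster somewhere in a family of maps. The plan produces such a family, states a hypothesis broad enough for any of its members to be cited in support, and does not say in advance which member counts.

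The consequence is that one surviving cluster in one of many real-versus-sham maps could be reported as bearing out the fMRI part of the hypothesis. If acupuncture and sham had identical central effects, that would happen much more often than the 5% attached to each map. This is separate from whether z > 2.3 is a good cluster-forming threshold, because the problem remains when every map holds its 5% exactly.

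**Working it through.** **The plan's own figure.** The only imaging error rate in the article is 5% per map. It gives no error rate for the fMRI hypothesis as a whole. The two agree only if there is a single real-versus-sham map: 1 − 0.95¹ = 5%.

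**Inputs from the article.** Two connectivity runs (REST, CONT), each analysed by seed correlation and by independent components; TASK runs with two explanatory variables; two scan days; 5% per map.

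**Inputs assumed.** The number of seeds s, the number of components m tested per run, and the number of TASK group contrasts t. Only real-versus-sham maps are counted. The regressions on clinical measures are left out because they do not compare the arms.

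**Number of maps.** k = 2 × (s + m) + t

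**Chance of at least one false map, independent maps.** P = 1 − 0.95^k

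| Assumed content | k | P |
|---|---|---|
| 1 seed, 1 component, 2 TASK contrasts | 2 × 2 + 2 = 6 | 26.5% |
| 2 seeds, 1 component, 4 TASK maps | 2 × 3 + 4 = 10 | 40.1% |
| 4 seeds, no components, 3 TASK contrasts | 2 × 4 + 3 = 11 | 43.1% |
| 4 seeds, 1 component, 4 TASK maps | 2 × 5 + 4 = 14 | 51.2% |
| 3 seeds, 10 components, 4 TASK maps | 2 × 13 + 4 = 30 | 78.5% |

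The first row is a floor, since the article speaks of seeds in the plural. The four seeds in the third and fourth rows borrow the regions discussed in the Discussion (anterior cingulate, insula, thalamus, hypothalamus); the article does not say these are the seeds.

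**Crossing point.** P exceeds 50% when k > ln 0.5 / ln 0.95 = 13.5, so from 14 independent maps. At 13 it is 48.7%.

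**Correlated maps.** The maps share participants and scan days, so independence is on the high side. Treat each map's false-positive event as one upper-tail 5% event of a normal variable, with common correlation ρ between maps. Then P = 1 − E[Φ((1.645 − √ρ·X)/√(1 − ρ))^k], with X standard normal.

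| k | ρ = 0 | ρ = 0.3 | ρ = 0.5 |
|---|---|---|---|
| 6 | 26.5% | 22.0% | 18.6% |
| 10 | 40.1% | 30.7% | 24.7% |
| 14 | 51.2% | 37.2% | 29.1% |

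Passing 50% now takes 16 maps at ρ = 0.1, 26 at ρ = 0.3 and 63 at ρ = 0.5.

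**Direction.** A threshold of z above 2.3 looks in one direction, the hypothesis names no direction, and the article does not say whether real > sham and sham > real are each thresholded at 5%. If they are, the number of tests doubles:
- 14 tests are reached with 7 contrasts.
- 8 contrasts make 16 tests, and 1 − 0.95¹⁶ = 56.0%.
- 11 contrasts make 22 tests, and 1 − 0.95²² = 67.6%. With correlated contrasts this falls to 54–61% at ρ = 0.3 and 45–51% at ρ = 0.5, depending on how the two directions of one contrast are tied together.

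If instead the 5% covers both directions of each contrast, 11 independent contrasts stay at 43.1%.

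**Size of a correction.** Bonferroni across maps would need 0.05/6 = 0.0083 per map for 6 maps and 0.05/14 = 0.0036 for 14. Holm starts at the same level for the smallest p-value and is then less strict.

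**The case against.** Four arguments stand against the point.

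1. **No decision rule is stated.** The article never says that a difference in any one map meets the hypothesis, and the hypothesis also rests on metabolomics. This stands: the percentages above are conditional on reading any surviving real-versus-sham map as support.

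2. **The map count is assumed.** A reader might infer that the rule would fire more often than not under an inert treatment. The article does not support that. It gives no count; more than half needs 14 independent maps, or about 7 or 8 contrasts with a full 5% in each direction, and several of the correlated cases stay below half. What survives is weaker but sufficient: even the smallest count gives about 19% to 27%.

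3. **The imaging is framed as exploration.** The Abstract and Discussion speak of exploring mechanism, the Discussion closes by expecting only a glimpse of it, the sample size section plays down formal power for fMRI, and no brain map is listed among the outcomes. This lowers the stakes. It does not withdraw the stated hypothesis, and nowhere are the maps labelled exploratory.

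4. **Contrasts and hierarchies are often left to a fuller protocol or analysis plan.** That is fair for detail about which the article is silent. Here the article is not silent: it sets the multiplicity rule for all brain maps, and that rule stops at the edge of each map.

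**Conclusion.** The point holds in a limited form. The article states a real-versus-sham mechanistic hypothesis, corrects for multiplicity only within maps, and does not say which map tests the hypothesis. If any surviving map were taken as support, the chance of at least one false one would be roughly 19% to 27% at the smallest count (6 maps; correlation 0.5 to independence) and 43% at 11 independent maps, passing 50% only from 14. These figures assume exactly 5% per map and assumed numbers of seeds, components and contrasts. Stronger correlation lowers them, and separate 5% tests in each direction raise them.

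The clinical primary outcome, the proportion of responders, is a single comparison and is not touched. The issue deserves a change of wording because the mechanistic claim is one of the trial's stated hypotheses, but it does not threaten the main efficacy result.

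**What to change.** In the fMRI data processing section, name one real-versus-sham contrast as the test of the fMRI part of the hypothesis. Examples are the between-arm difference in the TASK2 minus TASK1 change at one stated scan day, or the between-arm difference in the change in REST connectivity of one seed fixed before the data are seen. A seed drawn from the trial's own TASK results would not meet that condition.

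Alternatively, give a short closed list of contrasts with Holm correction across the list and across both directions.

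In either case, state that all other seeds, components, TASK maps and clinical regressions are exploratory and cannot on their own support the statement that a mechanistic difference exists.

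This costs wording only: no added scans, participants or data. The downside is that differences outside the named contrast or list can be reported only as exploratory, so fewer brain differences can be claimed as confirmed.
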